## **12.2 Grading of adverse events**

The medical investigator will attempt to identify all clinical and objective adverse events and establish their relationship to the study drug. Adverse events, if any, should be graded according to the following scale:

- 1 = slight
- 2 = moderate
- 3 = severe
- 4 = life-threatening

## **12.3 Reporting of AEs and SAEs**

The investigator has the responsibility to ascertain that all adverse events will be recorded and appropriately documented in the participant's Case Report Form. The Sponsor is responsible for the continuous evaluation of the study risk/benefit ratio. If a situation arises, that may affect the participants' safety or that affects the ethical integrity of the study, it must be immediately reported to the Danish Health and Medicines Authority. A similar report must be sent to all the involved investigators and to the regional Research Ethical Committee.

Furthermore, the following rules for reporting to authorities should be taken into account. Any significant side-effect caused by drugs given in the study – the experimental treatment, comparison

drugs or placebo – must be reported. The sponsor has to be kept informed by the investigator of adverse events. The final report of the study should contain a description of all observed side effects.

SAEs must be reported immediately by the investigator to the sponsor and in addition a report on participants' safety should be sent once per year to the Research Ethical Committee.

**Serious adverse reactions (SARs)** (Serious, suspected adverse reactions), and in addition a report on participants safety, should be reported by the sponsor once per year to the Danish Health and Medicines Authority.

The sponsor must immediately report unexpected and **serious suspected adverse events (SUSAR)** to the Danish Health and Medicines Authority. Summary of Product Characteristics of naloxone will be used as a reference document for evaluating whether a serious related adverse reaction is unexpected or expected. **Fatal or life-threatening SUSAR's** must be reported to the Danish Health and Medicines Authority with all relevant information including follow-up within 7 days after the sponsor became aware of them, and no later than 8 days after notification. All other unexpected and serious suspected adverse events should be reported to the same authorities within 15 days after the sponsor has become aware of them. Reports should be accompanied by comments on the consequences for the study. It is also recommended that the sponsor informs the drug manufacturer.

#### 12.4 Procedures in case of emergency

The investigator will ensure that there are planned procedures and the necessary expertise to deal with an emergency situation that may arise during the study. The randomization code (and thus the blinding procedure) should only be broken, if it is necessary to know which drug has been administered to the participant. Individual drug-packages include a sealed, non-transparent envelope containing the randomization sequence code for each participant (paragraph 10.2.1, page 26). This envelope is immediately broken by the investigator should an emergency arise that require un-blinding of the drug. If the code envelope is opened, the date and justification must be registered. The envelope must then be signed by the investigator and the participant will be excluded from the study.

### 13. STATISTICAL ANALYSES

#### 13.1 Sample size calculations

##### 13.1.1 TME-participants

Sample size calculations are based on following assumptions and estimations (abbreviations: BL = baseline; NX = naloxone; PL = placebo; TCI = during target-controlled-infusion):

1. a primary outcome based on a summed measure (SM) of resting pain (RP), masticatory pain (MP; (movement-related) and pressure-evoked pain (PM; pressure algometry [100 kPa]).  $NRS_{SM} = NRS_{RP} + NRS_{MP} + NRS_{PM}$ .
2. the summed pain intensities (SPIs) are calculated as: (BL-SPINX) and (TCI-SPINX), and, (BL-SPIPL) and (TCI-SPIPL), where (TCI-SPI) indicates SM-value at highest obtainable TCI-step (Fig. 2).
3. the summed pain intensity differences (SPIDs) are the differences: **SPIDNX** = (TCI-SPINX) – (BL-SPINX) and **SPIDPL** = (TCI-SPIPL) - (BL-SPIPL)

4. the mean [SD] BL-pain intensities are estimated to be: resting pain 1 [1] NRS-units; movement related pain 2 [2] NRS-units; pressure evoked pain 4 [2] NRS-units.
5. the mean [SD] summed BL-pain intensity (BL-SPI) is estimated to be 7 [4.1] NRS-units (Table 2).
6. the minimal relevant SPID-difference, calculated as  $\Delta SPID = SPID_{NX} - SPID_{PL}$  is estimated to be 5 (NX-group: RP = 4; MP = 5; PM = 7 [total 16]/PL-group: RP = 2; MP = 4; PM = 5 [total 11]) corresponding to a  $\Delta SPID\% = 45\%$ .
7. the design is a placebo-controlled, randomized, double-blind, crossover study
8. the significance level  $\alpha$  is set to 0.01 and the power is set to  $= 0.90$  ( $\beta = 0.10$ )

The total number of individuals estimated to be included in the study is calculatedE to be 14 (effect size 1.2). Using the range of variances in Table 2, it can be calculated that the number of individuals ranges from 9 to 19, with effect sizes of 1.7 to 1.0, respectively.

In order to allow for drop-outs the total number of individuals is set to 18. Due to the frail nature of the sample size estimates, an interim-analysis of the primary outcome, performed by an independent statistician, is made after per-protocol inclusion of 14 individuals. If the null hypothesis (no statistical difference between the placebo and the naloxone groups) is rejected, the study is deemed completed. If the new sample size estimates indicate that more than 16 additional individuals (total number of individuals > 30) are required, the study is prematurely discontinued. If less than 16 additional individuals (total number of individuals  $\leq 30$ ) the study continues and is discontinued after the stipulated number has been reached.

| V(X1) | V(X2) | V(X3) | COV(X1,X2) | COV(X1,X3) | COV(X2,X3) | V(SUM) | SD(SUM) | CORR(X1,X2) | CORR(X1,X3) | CORR(X2,X3) |
|-------|-------|-------|------------|------------|------------|--------|---------|-------------|-------------|-------------|
| 1     | 4     | 4     | 0          | 0          | 0          | 9      | 3.00    | 0           | 0           | 0           |
| 1     | 4     | 4     | 0.1        | 0.1        | 0.2        | 9.8    | 3.13    | 0.05        | 0.05        | 0.05        |
| 1     | 4     | 4     | 0.2        | 0.2        | 0.4        | 10.6   | 3.26    | 0.1         | 0.1         | 0.1         |
| 1     | 4     | 4     | 0.3        | 0.3        | 0.6        | 11.4   | 3.38    | 0.15        | 0.15        | 0.15        |
| 1     | 4     | 4     | 0.4        | 0.4        | 0.8        | 12.2   | 3.49    | 0.2         | 0.2         | 0.2         |
| 1     | 4     | 4     | 0.5        | 0.5        | 1          | 13     | 3.61    | 0.25        | 0.25        | 0.25        |
| 1     | 4     | 4     | 0.6        | 0.6        | 1.2        | 13.8   | 3.71    | 0.3         | 0.3         | 0.3         |
| 1     | 4     | 4     | 0.7        | 0.7        | 1.4        | 14.6   | 3.82    | 0.35        | 0.35        | 0.35        |
| 1     | 4     | 4     | 0.8        | 0.8        | 1.6        | 15.4   | 3.92    | 0.4         | 0.4         | 0.4         |
| 1     | 4     | 4     | 0.9        | 0.9        | 1.8        | 16.2   | 4.02    | 0.45        | 0.45        | 0.45        |
| 1     | 4     | 4     | 1          | 1          | 2          | 17     | 4.12    | 0.5         | 0.5         | 0.5         |
| 1     | 4     | 4     | 1.1        | 1.1        | 2.2        | 17.8   | 4.22    | 0.55        | 0.55        | 0.55        |
| 1     | 4     | 4     | 1.2        | 1.2        | 2.4        | 18.6   | 4.31    | 0.6         | 0.6         | 0.6         |
| 1     | 4     | 4     | 1.3        | 1.3        | 2.6        | 19.4   | 4.40    | 0.65        | 0.65        | 0.65        |
| 1     | 4     | 4     | 1.4        | 1.4        | 2.8        | 20.2   | 4.49    | 0.7         | 0.7         | 0.7         |
| 1     | 4     | 4     | 1.5        | 1.5        | 3          | 21     | 4.58    | 0.75        | 0.75        | 0.75        |
| 1     | 4     | 4     | 1.6        | 1.6        | 3.2        | 21.8   | 4.67    | 0.8         | 0.8         | 0.8         |
| 1     | 4     | 4     | 1.7        | 1.7        | 3.4        | 22.6   | 4.75    | 0.85        | 0.85        | 0.85        |
| 1     | 4     | 4     | 1.8        | 1.8        | 3.6        | 23.4   | 4.84    | 0.9         | 0.9         | 0.9         |
| 1     | 4     | 4     | 1.9        | 1.9        | 3.8        | 24.2   | 4.92    | 0.95        | 0.95        | 0.95        |
| 1     | 4     | 4     | 2          | 2          | 4          | 25     | 5.00    | 1           | 1           | 1           |

**Table 2.** The variance (V) of the summed pain intensity (SPI) is:

$$V_{SPI} = V_{RP} + V_{MP} + V_{PM} + 2*(COV(RP,MP) + COV(RP,PM) + COV(PM,MP))$$

However, the covariances are unknown, but the table illustrates the relationship between  $V_{SPI}$  (blue column;  $SD_{SPI}$  green column) vis-à-vis different correlations between the variables (RP, MP, PM). A correlation estimate between the variables of 0.5 was used.

E G\*Power version 3.9.1.2, University of Kiel, Germany

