## 13.2 Data processing

### 13.2.1 TME-participants

To test if data is normally distributed, residual plots and the Kolmogorov-Smirnov test will be used (SPSS 20.0, Chicago, IL, USA; MedCalc Software: version 12.07.0.0; Mariakerke, Belgium). In case of non-normal data distribution, primarily a logarithmic transformation is tried or secondarily a Box-Cox transformation will be attempted for normalization of data.

The primary outcome  $\Delta\text{SPID}$  ( $\text{SPID}_{\text{NX}} - \text{SPID}_{\text{PL}}$ ) is analyzed by one-way repeated measures ANOVA ( $\Delta\text{SPID}$ : dependent variable; TCI-steps: independent variable) or a corresponding non-parametric analogue (Friedman test), as appropriate. Paired  $t$ -test or Wilcoxon rank sum test will be used, as appropriate for inter-group comparisons.

A mixed model with random effect for subject and fixed-effects for the factors; *target-controlled-infusion* (step 1/step 2/step 3), *drug* (naloxone/placebo); *secondary hyperalgesia area* (SHA); *pressure pain threshold* (PPT); *HADS-score*; and *PCS-scores*, are used for the primary outcome  $\Delta\text{SPID}$  ( $\text{SPID}_{\text{NX}} - \text{SPID}_{\text{PL}}$ ). Non-significant ( $P > 0.05$ ) factors, beginning with interactions, are excluded until all included factors attain significance. Main-effects and interaction-effects are examined.

The risk of type I error is reduced by setting a significance level of 0.01 ( $\alpha$ ). A power of 0.90 ( $\beta = 0.10$ ) is set in order to reduce the risk of type II errors. For all statistical calculations, in which multiple comparisons are performed, Duncan's new multiple range test or Scheffé's method, as appropriate, will be used. Statistical calculations will be performed with partially un-blinded data, i.e., group A and B. When statistics have been completed, data are unblinded, into naloxone and placebo groups.

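### The TME sample size divides an effect on a difference of changes (ΔSPID) by the SD of one baseline score, so 90% power with 14 subjects does not follow from the stated inputs

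*Protocol*

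**What the plan says.** All places are in the Protocol.

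- **Endpoint (13.1.1, items 1 to 3).** Resting, masticatory and pressure-evoked pain are added to a summed score (SPI). "the summed pain intensity differences (SPIDs) are the differences" between the infusion and baseline SPI of the same day, one for naloxone and one for placebo.
- **Effect (13.1.1, item 6).** The minimal relevant ΔSPID = SPID_NX − SPID_PL "is estimated to be 5 (NX-group: RP = 4; MP = 5; PM = 7 [total 16]/PL-group" with a total of 11).
- **SD (13.1.1, item 5).** "the mean [SD] summed BL-pain intensity (BL-SPI) is estimated to be 7 [4.1] NRS-units (Table 2"). Table 2 builds this from component SDs of 1, 2 and 2. Its note says: "A correlation estimate between the variables of 0.5 was used". The variables are the three pain components.
- **Error rates (13.1.1, item 8; repeated in 13.2.1).** α "is set to 0.01 and the power is set to" 0.90. Sidedness is not stated.
- **Result (13.1.1).** The number of individuals is calculated "to be 14 (effect size 1.2"). Over the variances in Table 2, "the number of individuals ranges from 9 to 19, with effect sizes of 1.7 to 1.0, respectively".
- **Interim (13.1.1).** The protocol calls its estimates frail. An independent statistician analyses the primary outcome at 14 subjects, and the trial may then be re-sized up to a total of 30. Section 6.1 gives a maximum included number of 18.

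**The concern.** The numerator and the denominator of the effect size belong to different quantities. The 5 is a difference of two changes and involves four summed scores. The 4.12 is the SD of one summed score at baseline. The two SDs agree only under particular correlations between the four scores, and the protocol states none of them.

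The quoted range of 9 to 19 looks like a sensitivity analysis for this uncertainty, but it varies only the correlation among the three pain components within one score. It does not touch the missing quantity.

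This calculation is the only justification for the TME sample size and for placing the interim look at 14. If it stands as written, a null result could be cited as a negative with 90% power when the protocol gives no basis for that figure.

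**Working it through.** **Step 1. The SD used.** With component variances 1, 4 and 4 and correlation 0.5, the covariances are 1, 1 and 2. Var(SPI) = 1 + 4 + 4 + 2 × (1 + 1 + 2) = 17, so σ = √17 = 4.12. This is the SD of one SPI.

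**Step 2. Reproducing the plan's figures.** Paired t-test, non-central t, α = 0.01 two-sided, power 0.90, effect size = 5/SD:

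| SD | 5/SD | n | Protocol |
|---|---|---|---|
| 4.12 | 1.21 | 14 (power 0.913) | 14, effect size 1.2 |
| 3.00 | 1.67 | 9 | 9, effect size 1.7 |
| 5.00 | 1.00 | 19 | 19, effect size 1.0 |

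All three match. A one-sided test would give 12 instead of 14, so the calculation was two-sided and used the single-score SD as the SD of ΔSPID.

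**Step 3. The SD that belongs to the effect.** Write T for an infusion score and B for a baseline score. Then ΔSPID = (T_NX − B_NX) − (T_PL − B_PL). Let the SD be σ at all four assessments, and let r be the correlation of T and B on the same day. Let e be the average of the T-T and B-B correlations across days, minus the average T-B correlation across days. Then

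Var(ΔSPID) = 4σ²(1 − r − e).

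If all cross-day correlations are equal, e = 0 and Var(ΔSPID) = 4σ²(1 − r). This equals σ² only when r = 0.75.

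**Step 4. Consequences with e = 0 and σ = 4.12.**

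| r | SD(ΔSPID) | Power at n = 14 | n for 90% |
|---|---|---|---|
| 0.5 | 5.83 | 59% | 24 |
| 0.6 | 5.22 | 71% | 20 |
| 0.7 | 4.52 | 85% | 16 |
| 0.75 | 4.12 | 91% | 14 |
| 0.8 | 3.69 | 96.5% | 12 |

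The smallest r that gives 90% power is 0.74 with 14 subjects and 0.64 with 18. At r = 0.5 and r = 0.6 the required n lies above the protocol's range of 9 to 19.

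**Step 5. Relaxing the simplifications.**

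- *Unequal cross-day correlations.* With e = 0.1, r of about 0.64 is enough for 90% power at n = 14; with e = 0.25, about 0.49. For example, r = 0.5 with same-state cross-day correlation 0.5 and cross-state 0.25 gives Var = 4 × 17 × (1 − 0.5 − 0.25) = 17, and power is again 91%.
- *Larger SD during infusion.* If it is k times the baseline SD on both days and cross-day correlations are equal, Var = 2σ²(1 + k² − 2rk). With k = 1.25 and r = 0.75 this is 34 × (1 + 1.5625 − 1.875) = 23.4, SD 4.83. Power at n = 14 is 79% and 18 subjects are needed. Item 6 plans a naloxone mean of 16 against a baseline of 7, so an equal SD cannot be taken for granted.

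The protocol fixes neither e nor k.

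**The case against.** **A reader might infer that the 90% holds only if r is about 0.75, or that the true power is near 60%.** The documents support neither. The 0.75 condition needs equal SDs and equal cross-day correlations, and step 5 shows a structure with r = 0.5 that still gives 91%. Nothing in the protocol singles out r = 0.5 either: the 0.5 in the note to Table 2 concerns the three pain components of one score.

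**The interim look.** Failure to reject at 14 does not by itself end the trial. The 24 subjects needed at r = 0.5 lie within the cap of 30. A simulation that re-estimates n from the observed SD of ΔSPID with the effect held at 5, and tests at 0.01 both times, gives overall power of about 79%, 89% and 95% at r = 0.5, 0.6 and 0.7 with e = 0. Part of this comes from testing twice. This stands: 59% describes the first look only. Three limits remain:

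- The re-estimation does not make 14 follow from the inputs.
- Section 13.1.1 does not say which SD the new estimate uses, so repeating the single-score SD would repeat the error.
- The total of 30 does not match the maximum of 18 in section 6.1. With 18 subjects, power at r = 0.5 and e = 0 is 76%.

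**The matter could be left to a statistical analysis plan.** It could not here, because the protocol itself states the SD, effect size, n and power. The point concerns a stated calculation, not an omitted detail.

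**Conclusion.** The point holds in a bounded form. That the SD of one baseline summed score was used as the SD of ΔSPID is certain, since all three sample sizes reproduce with it. The unconditional 90% power at n = 14 is therefore unsupported. It is not shown to be false, because it would be met under some plausible correlations and missed under others.

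With equal SDs at all four assessments and equal cross-day correlations, power at n = 14 runs from 59% to 96.5% as r goes from 0.5 to 0.8. A higher same-state than cross-state correlation between days lowers the r required, and a larger SD during infusion raises it. The interim re-estimation reduces the practical harm without repairing the calculation.

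**What to change.** **Needed (text of 13.1.1 only):**

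1. Base the effect size on an assumed SD of ΔSPID, and state the within-day and between-day correlations behind it.
2. Show power at n = 14 over a range of these correlations, including r = 0.8, and put this conditional statement in place of the unconditional 90%.
3. State that the interim re-estimation uses the observed SD of ΔSPID.

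This adds no subjects. The cost is that the stated power becomes conditional and, over part of the range, less favourable.

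**Optional:** analyse the naloxone-minus-placebo difference in infusion SPI with the difference in same-day baseline SPI as covariate, instead of subtracting the baselines. This costs one degree of freedom and a revision of 13.2.1, where ΔSPID is the outcome of both the repeated-measures ANOVA and the mixed model. In simulations at n = 14 the gain depended on the correlations. It ranged from about 2 points (91% to 93%) to about 28 points (59.2% to 87.5%, with all pairwise correlations 0.5), so the larger figure should not be quoted as the expected benefit.

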## **6. STUDY DESIGN**

### **6.1 TME-participants**

|                |                                                                                                  |
|----------------|--------------------------------------------------------------------------------------------------|
| Study type:    | Randomized, placebo-controlled, double-blind crossover                                           |
| Randomization: | Computer generated randomization list, closed envelopes                                          |
| Phase:         | Phase 2                                                                                          |
| Blinding:      | Double-blind, crossover                                                                          |
| Subjects:      | Participants with unilateral, primary, uncomplicated, impacted mandibular third molar extraction |
| Number:        | 14 evaluable subjects (maximum included number: 18)                                              |

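### The TME interim rule allows two tests at a single stated level of 0.01, does not say what is re-estimated, and permits 30 participants where section 6.1 caps inclusion at 18

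*Protocol*

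**What the plan says.** Section 13.1.1 plans 14 participants in a crossover for a difference in ΔSPID that "is estimated to be 5 (NX-group: RP = 4; MP = 5; PM = 7 [total 16]/PL-group" and so on, with an SD of 4.1 (4.12 in Table 2), α = 0.01 and power 0.90. It allows for drop-outs: "In order to allow for drop-outs the total number of individuals is set to 18". Because the estimates are called frail, an independent statistician analyses the primary outcome once 14 participants are included per protocol. Three outcomes follow.

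- "If the null hypothesis (no statistical difference between the placebo and the naloxone groups) is rejected, the study is deemed completed".
- If the new estimate requires a total above 30, the study is discontinued.
- If the new total is 30 or less, the study continues to that number.

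Section 13.2.1 repeats the single level: "The risk of type I error is reduced by setting a significance level of 0.01". No separate level is given for the interim test or for the test after extension. The text does not say whether the new estimate uses the observed effect or only an updated SD. Section 6.1 gives the TME number as "14 evaluable subjects (maximum included number: 18").

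**The concern.** Rejection at 14 ends the study with a positive result, and non-rejection can lead to more data and another test. Two chances to reject, each at 0.01, give an overall error above 0.01 unless something is adjusted. The protocol relies on the strict 1% level as its protection against false positives.

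The re-estimation decides whether a non-significant trial is extended or abandoned. Its input is not named, and the two plausible inputs give very different behaviour. Choosing between them after 14 treatment differences have been analysed could not be defended as pre-specified.

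The extension also needs up to 30 participants, while section 6.1 gives 18 as the most that may be included.

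**Working it through.** **Inputs.** Δ = 5, SD 4.12 (Table 2, correlation 0.5), α = 0.01 and power 0.90, all from section 13.1.1. The test is paired. Sidedness is not stated; two-sided is used because it reproduces the plan's numbers.

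**Plan's own figure.** Take the smallest n at which the noncentral t with n − 1 df and noncentrality (Δ/SD)√n exceeds t(0.995, n − 1) with probability at least 0.90.

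- SD 4.12: 5/4.12 = 1.21, n = 14.
- SD 3: 5/3 = 1.67, n = 9.
- SD 5: 5/5 = 1.0, n = 19.

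These match the stated 14 and the range 9 to 19. One-sided testing would give 12, 8 and 16.

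**Interim rejection limit.** t(0.995, 13) = 3.012, so rejection needs an observed effect size above 3.012/√14 = 0.805.

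**Region that leads to extension.**

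- *Observed effect:* a required total of 30 or less needs an observed effect size of at least 0.748. Extension occurs only between about 0.75 and 0.805.
- *SD only, Δ = 5:* a required total of 30 or less needs an observed SD of at most 5/0.748 = 6.7, so far more non-significant trials are extended.

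**An assumed larger SD.** The 4.12 is the SD of one baseline sum, whereas ΔSPID combines four such sums. If each has SD 4.12 and any two correlate at ρ, SD(ΔSPID) = 2 × 4.12 × √(1 − ρ). This is 4.12 at ρ = 0.75 and 5.83 at ρ = 0.5. This ρ is not in the protocol, and it is a different correlation from the 0.5 in Table 2, which is between the three pain components. The 5.83 is therefore an assumption.

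**Overall type I error**, both looks at 0.01 (1,000,000 simulated trials per case):

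| Rule after non-rejection | SD 3 | SD 4.12 | SD 5 | SD 5.83 (assumed) |
|---|---|---|---|---|
| Observed effect | 1.05% | 1.05% | 1.05% | 1.05% |
| SD only, Δ = 5 | 1.0% | 1.0% | 1.3% | 1.5% |
| Every non-rejection goes to 30 | 1.8% | 1.8% | 1.8% | 1.8% |

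The first row is rounded; single runs lay between 1.04% and 1.07%. A bivariate normal calculation with information fraction 14/30 gives 1.79% for the last row.

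**Behaviour at a true difference of 5**, where abandoned means stopped because the new total exceeds 30:

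| | SD 4.12 | SD 5 | SD 5.83 (assumed) |
|---|---|---|---|
| Rejected at n = 14 | 91% | 75% | 59% |
| Observed effect: abandoned | 6% | 19% | 34% |
| Observed effect: overall power | 94% | 81% | 66% |
| SD only: abandoned | 0.1% | 3% | 14% |
| SD only: overall power | 97% | 91% | 79% |

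**A case the rule does not address.** With SD-only re-estimation, a trial can be non-significant while its new total is 14 or fewer. This happens in about 59% of null trials at SD 4.12, and the protocol does not spell out what follows.

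**The maximum.** 14 + 16 = 30, which is 12 more than the 18 in section 6.1.

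**The case against.** **The protocol points towards SD-only re-estimation.** It calls 5 the minimal relevant difference, says the covariances are unknown, and varies only the variance to reach 9 to 19. On that reading extension is common: about 40% of null trials at SD 4.12 and 72% at SD 5. This stands. A reader might infer that the extension rule almost never operates, but that holds only under the observed-effect reading, which the document does not state. What remains is that the protocol does not say which reading is meant.

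**The inflation is small.** This also stands. A reader might infer that the error nearly doubles to 1.8%, but that requires every non-rejection to continue to 30, and the protocol prescribes no such thing. Where extension is rare, the inflation is negligible.

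**The worst power figures rest on an imported SD.** Correct. A reader might infer that a third of worthwhile trials are abandoned. That needs both the observed-effect reading and the assumed 5.83; at the protocol's own 4.12 the figure is 6%.

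**An interim level may stand in an analysis plan that is not shown.** That is possible, and testing at the full level is an inference from 0.01 being the only level given. However, the protocol itself fixes the early stop and supplies one level for it.

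**18 and 30 can be read in sequence**, as a base plan and a conditional extension. Within 13.1.1 that is fair. The reimbursement line in section 15.2 (18 × 6 h × 150 DKR = 16,200 DKR) shows only that the base plan was priced, in a budget labelled preliminary. Section 6.1, however, calls 18 the maximum and does not mention the extension.

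**Conclusion.** The point holds, at moderate weight: it should be fixed, but it does not undermine the trial.

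- The 1% error is not strictly held. Over Table 2's SDs of 3 to 5 the overall error is about 1.0-1.3%, and about 1.5% at the assumed 5.83 with SD-only re-estimation.
- The unnamed re-estimation input matters more. At a true difference of 5, the choice moves overall power by 3 percentage points at SD 4.12 (94% or 97%), 10 at SD 5 (81% or 91%) and 13 at the assumed 5.83 (66% or 79%).
- The maxima of 18 and 30 contradict each other as written and need no calculation.

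These figures assume two-sided paired t-tests on normal differences, the same 0.01 at both looks, and pooling of all participants at the second look.

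**What to change.** 1. State in 13.1.1 that the independent statistician re-estimates only SD(ΔSPID), keeping Δ = 5, and that a non-significant trial whose re-estimated total is 14 or fewer ends there. In the same edit, assign exactly 16 additional participants to continuation in words, as the bracketed limit already does.
2. Choose one testing scheme:
   - *No significance test at n = 14, and one final test at 0.01.* This gives up the early stop. Re-using the SD that set the sample size leaves a small residue: repeating the simulation without the interim test gave 1.0% at SD 3 and 4.12, 1.15% at SD 5 and 1.2% at 5.83.
   - *Each look at a nominal level of about 0.005.* The overall error is about 0.93% for looks at 14 and 30; a normal approximation allows about 0.0055. The cost is power at n = 14, which falls from 91% to 85% at the design effect.
3. Amend 6.1 so that 18 is the initial number and 30 the maximum after the interim, or remove the extension from 13.1.1.

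All of this is protocol wording, and it should be settled before the interim data are analysed.
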